### Analyses

Data records from the different tests and questionnaires will be collected and merged into one database. The database management will be done by the project team and handled according to the internal regulations of the UMCG. The analyses of the study will be performed with SPSS software version 22.0 (IBM).

Before any analysis, data will be prepared:

Variables need to be calculated: body mass index; DMA, WUR and CPM tests (see the Methods and analyses section, Measurements: CS measurements); PDI, Rand36-PF, PCS, BSI and IEQ questionnaires.HRV: data will be preprocessed to correct for any artefacts that may be present at the beginning or at the end of the recording.QST: the overall value of each sensory test is the mean at the most painful location and the five control locations together, provided that at most two locations are missing.To perform the analyses to respond to objective 3, delta scores are computed (difference in scores between baseline and discharge) for CS, functioning and those confounder variables which are also measured at the same time points as the main measurements.

Proxies of the main measurements were selected to perform analyses. CS variables are: the sum score of CSI part A and the RMSSD for HRV. For QST, no variables are predefined, variables that correlate most strongly with each of the functioning measures will be selected. Functioning variables are: the maximal weight lifted for lifting capacity, the VO_2_max/kg for the maximal aerobic capacity, the daily vector magnitude (VM) counts for PA and the average score of Rand36-PF for reported physical functioning.

The presence of missing data will be checked. If a variable has more than 10% of missing data cases, its distribution will be further examined. When the distribution of missing data is missing completely at random, analyses with pairwise deletions are planned. If data are not missing completely at random, other suitable solutions will be applied such as multiple imputation.^91^ Regarding the presence of outliers, cases at 3 SD from the mean will be considered as outliers. Their influence will be measured using Cook’s distance and leverage values. When the outliers are not statistically influential and/or there is rationale for the outlier, no further actions are planned. The descriptive statistics of the sample characteristics and main test results will be at this point calculated; numerical variables as mean and SD in normally distributed data and as median and IQR (25–75)) in non-normally distributed data, and categorical variables as counts and percentage of each category level.

*Statistical approach for objective 1: to analyse the association between instruments assessing reference symptoms and signs attributed to CS.* Multiple partial correlation analyses will be performed and corrected for potential confounders. CS measurements will be the main variables and sex and age will be covariates. Additional covariates may enter the partial correlations based on their correlation coefficient with CS instruments and if p<0.01. Results will be reported as correlation coefficients (Pearson’s r and/or Spearman’s rho) and p values, with and without controlling for covariates. The significance level for all analyses is established at 0.01, to account for the potential type I error due to the multitude of partial correlation analyses.
*Statistical approach for objective 2: to analyse whether reference symptoms and signs attributed to CS are associated with functioning measurement outcomes.* First, multiple correlation analyses, followed by multiple regression analyses with data obtained at baseline, will be performed. Each of the main outcomes from functioning measurements will be introduced in the models as dependent variable, CS measurements as independent variables, and sex, age and other demographic characteristics and/or test-related variables as potential confounders and/or moderators.
*Statistical approach for objective 3: to analyse whether changes (between baseline and discharge) in reference symptoms and signs attributed to CS are related to changes in each of the functioning measurement outcomes.* A similar approach to objective 2 will be performed: first, multiple correlation analyses will be performed with data obtained at baseline and discharge, followed by multiple correlation analyses using delta scores of the data and, finally, multiple regression analyses again using delta scores. As in objective 2, each of the main outcomes from functioning measurements will be introduced in the models as dependent variable, CS measurements as independent variables, and sex, age and other demographic characteristics and/or test-related variables as potential confounders and/or moderators.

Confounders entering the final models of objectives 2 and 3 will be selected based on their partial correlation coefficient with CS and functioning, and they will be included if p≤0.10. All multiple regression models will have the assumptions checked. Results of objectives 2 and 3 will be reported as coefficient (b), CIs (95% CI), p values and explained variance, with and without controlling for confounders and/or moderators. Due to the large amount of correlation analyses and the risk of high type I error, a stricter significance level for correlation analyses is established, p<0.01. For multiple regression analyses the significance level is at 0.05.

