##### Heart rate variability

The test provides an indication of the function and balance of the autonomic nervous system (ANS), which is responsible for the control of internal functions including self-regulation, adaptability and resilience capacities.^57^ The ANS is susceptible to mental and emotional processes, which in turn can produce an imbalance in self-regulation (affecting, among others, heart rate (HR)) by a hyperactivation of the sympathetic tone and reduced parasympathetic/vagal tone.^15 34^ HRV testing can monitor heart rhythms, or time and pattern variation on HR and interbeat (RR) intervals, and can be used to assess the function of the ANS.^58 59^ The HRV test is performed by assessors trained by the HeartMath Institute, and the 5 minute protocol is executed to guarantee the comparison of the results as recommended by the task force for short-term recordings.^58^ Patients are instructed to sit calmly and breathe normally, while they have an ear pulse sensor placed which is connected to a computer.^60^ The following measures are collected and recorded with the emWave PC software (emWave, HeartMath, Boulder Creek, California, USA): mean HR in beats per minute, mean RR interval in milliseconds; time domain measures in milliseconds as SD of normal-to-normal interval indicator for cyclic components responsible of RR interval variability, root mean square of successive differences (RMSSD) for beat-to-beat variance in HR and parasympathetic/vagal tone; frequency domain measures in ms^2^/Hz as very-low-frequency (0.0033–0.04 Hz) indicator for long-term regulation and sympathetic tone, low frequency (0.04–0.15 Hz) for sympathetic and parasympathetic/vagal tones and high frequency (0.15–0.40 Hz) for parasympathetic/vagal tone related to breathing rate; and normalised coherence indicator for HRV stable or regular pattern over time in percent, where higher scores mean more harmonic signal.

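### The stated HRV artefact rule reaches only the two ends of the recording, while RMSSD, the only HRV variable analysed, is sensitive to a single bad beat anywhere in it

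*Protocol article*

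**What the plan says.** The Heart rate variability section describes a short recording made while the patient sits calmly: "the 5 minute protocol is executed to guarantee the comparison of the results". The signal is a pulse wave, since "they have an ear pulse sensor placed which is connected to a computer", and the measures are collected with the manufacturer's software. They include "root mean square of successive differences (RMSSD) for beat-to-beat variance in HR and parasympathetic/vagal tone" and other time- and frequency-domain measures.

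The Analyses section names the variables that enter the models: "CS variables are: the sum score of CSI part A and the RMSSD for HRV". So RMSSD is the only HRV variable analysed, although others are collected. The same section gives the HRV preparation rule: "data will be preprocessed to correct for any artefacts that may be present at the beginning or at the end of the recording". It then sets a general outlier rule: "cases at 3 SD from the mean will be considered as outliers", followed by Cook's distance and leverage, and "When the outliers are not statistically influential and/or there is rationale for the outlier, no further actions are planned".

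**The concern.** The article states an artefact rule and gives its scope as the two ends of the recording. That scope fits RMSSD poorly. A missed beat merges two intervals into one of about twice the length and creates two very large successive differences, which RMSSD then squares. Trimming or cleaning the ends cannot remove such a beat from the middle.

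RMSSD represents HRV in all three objectives. Noise in it weakens its partial correlations with CSI and QST (objective 1) and its regression coefficients for functioning (objective 2). It enters the objective 3 delta scores twice, once per visit. The error also has a direction: a missed beat raises RMSSD, and objective 3 reads a rise in vagal tone as a decrease in central sensitisation.

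**Working it through.** **Plan's own figure.** None exists. The article gives no mean RR interval, RMSSD or artefact rate, so these are assumptions below and are shown as ranges.

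**Inputs from the article.** Recording length 300 s; RMSSD as the analysed variable; planned correlation 0.25; correlation significance level 0.01; sample size 110.

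**Effect of one missed beat.** With mean interval RR there are n = 300 s / RR intervals. One missed beat leaves n − 1 intervals and n − 2 differences, two of which are about +RR and −RR. Hence

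RMSSD_obs = √(RMSSD² + 2·RR²/(n − 2)).

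At RR 800 ms, n = 375 and the added term is 2 × 800² / 373 = 3,432 ms², equivalent to 58.6 ms in quadrature.

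| True RMSSD (ms), RR 800 | Observed (ms) | Factor |
|---|---|---|
| 20 | 61.9 | 3.10 |
| 30 | 65.8 | 2.19 |
| 40 | 70.9 | 1.77 |
| 50 | 77.0 | 1.54 |
| 60 | 83.9 | 1.40 |
| 80 | 99.2 | 1.24 |

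The factor is exactly 2 when the true RMSSD equals the added term divided by √3: 58.6/√3 = 34 ms at RR 800, 28 ms at RR 700 and 47 ms at RR 1000. Over RR 700–1000 ms and RMSSD 15–80 ms the extremes are:

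- RR 700, RMSSD 80: √(6,400 + 2,300) = 93.3 ms, factor 1.17.
- RR 1000, RMSSD 15: √(225 + 6,711) = 83.3 ms, factor 5.55.

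Simulated autocorrelated recordings (2,000 per setting) gave factors of 3.10, 2.20 and 1.78 at RR 800 with RMSSD 20, 30 and 40, in agreement with the formula. In the same simulation an ectopic beat arriving 30% early had a smaller effect: 1.82, 1.43 and 1.26.

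**Would the 3 SD rule catch it?** Assume lognormal RMSSD across patients (median 28 ms, log-SD 0.5), RR 800 ms, and one missed beat in a share of recordings.

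| Share affected | 3 SD cut (ms) | Affected recordings above the cut |
|---|---|---|
| 5% | 88.9 | 4.0% |
| 10% | 94.3 | 2.5% |
| 20% | 103.2 | 1.3% |
| 30% | 110.0 | 0.8% |

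At 10%, a contaminated recording exceeds the cut only if its true RMSSD is above √(94.3² − 3,432) = 74 ms.

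**Effect on correlations.** With the same model at 10% affected, observed and true RMSSD correlate 0.83, so 0.25 appears as 0.25 × 0.83 = 0.21. Widening to medians of 28–42 ms and RR of 800–857 ms gives:

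| Share affected | A true 0.25 appears as |
|---|---|
| 2% | 0.24–0.25 |
| 10% | 0.20–0.23 |
| 30% | 0.15–0.21 |

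For scale, approximate two-sided power at 0.01 with n = 110 is Φ(atanh(r)·√107 − 2.576). This is 0.53 at r = 0.25, 0.44 at 0.23 and 0.32 at 0.20.

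**Delta scores.** Assume also a baseline–discharge correlation of 0.7 on the log scale. At 10% affected, the observed change correlates 0.59–0.84 with the true change, against 0.78–0.94 for a single visit.

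**The case against.** The strongest reply is that the article does not say interior beats go uncorrected. The rule is one clause in a condensed article, the measures come from dedicated software run by trained assessors, and one collected measure is labelled "SD of normal-to-normal interval indicator for cyclic components responsible of RR interval variability", which hints at beat selection. If the software already removes abnormal beats, cleaning the ends is an extra step and the concern falls away. This stands as a limit. A reader might infer that mid-recording artefacts are left in, but the article neither states nor excludes filtering, and the normal-to-normal label defines no rule. The point still differs from an omitted detail, because the article does state an artefact rule and its stated scope is too narrow for RMSSD.

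A second reply is that the size is assumed. This also stands. A reader might take one missed beat to double RMSSD in general, but that holds only near a true RMSSD of 28–47 ms, depending on heart rate. A reader might also infer that HRV will falsely appear unrelated to central sensitisation. At 2% affected recordings the loss is negligible, and at 10% it is moderate. Losing the association would need frequent or multiple artefacts, and nothing in the article gives a rate; patients sit calmly.

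Third, RMSSD should not be described as one of exactly three predictors in every model. The Sample size section foresees at least three central sensitisation measurements, and the number of QST variables is left open.

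**Conclusion.** The point holds in limited form. The artefact rule as written does not reach the interior of the recording, no other part of the article covers it, and the patient-level outlier rule is not a substitute. The per-beat inflation of about 1.2 to 5.5 follows from the definition of RMSSD under the assumed heart rates and true values. The damage to the results depends on an unknown artefact frequency. At an assumed one bad beat in 10% of recordings it is a moderate attenuation, from 0.25 to about 0.20–0.23, with greater loss in the delta scores. That matters in a study that plans for weak correlations and tests them at 0.01, but it does not by itself invalidate the HRV results. Confidence is medium, because undocumented software filtering could remove the problem.

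**What to change.** Apply artefact detection and correction to the whole RR series before computing RMSSD, or confirm and state that the recording software already does so and by what rule. Fix in advance the criterion for an abnormal interval and the maximum share of corrected beats. A deviation of more than a set percentage from a local median, with a limit such as 5%, would be one workable choice; both are examples and are not taken from the article. Apply the rule blind to the other measurements, report the share of beats corrected at each visit, and set HRV to missing above the limit, so that it falls under the existing missing-data plan.

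The cost is reprocessing of the RR series, which is possible only if they were stored, and the loss of a few recordings.

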*Dynamic mechanical allodynia* (*DMA*)—to test the presence of abnormal stimuli-evoked pain—is assessed with a soft brush (SENSElab, Brush-05, Somedic, Hörby, Sweden) that is swiped 1–2 cm over the skin. This is performed on a single repetition and on a train of three repetitions (wind-up response). At each of the seven body locations (see online supplementary material 1) it is recorded whether the patients feel the sweeping and its pain intensity with a numeric rating scale (NRS) ranging from 0 (no pain) to 100 (most intense pain imaginable) for both the single swipe and the series.^45 46^ The DMA (ratio) is calculated as: DMA=(NRS-3/NRS-1). If NRS-1 is 0, the DMA for that location cannot be calculated and it will be registered as a missing value. The DMA test according to the DFNS protocol has shown to have good test–retest (r=0.87) and interobserver reliability (r=0.79).^44^

*Mechanical pain threshold* (*MPT*)—to test the ability to perceive sharp, pricking or stinging stimuli—is assessed with a set of standardised weighted pinprick stimulators with seven different intensities (the PinPrick Stimulator Set, MRC Systems, Germany) and with a modified method of limits. Starting at the lowest intensity (8 mN), it progressively increases until patients report the stimulus to change from touch to painful (sharp, pricking or stinging). The intensity of the pinprick that produces the first painful stimulus in millinewtons is recorded in each of the seven locations (see online supplementary material 1).^46–49^ The MPT test according to the DFNS protocol has shown to have good test–retest (r=0.80) and interobserver reliability (r=0.80).^44^

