*Wind-up ratio* (*WUR*)—to test the nervous system’s painful stimuli temporal summation or responsiveness to repeated noxious stimuli. Such test is assessed with a suprathreshold pinprick stimulator of 256 mN (the PinPrick Stimulator Set, MRC Systems, Germany), which is applied on a single repetition and on a train of 10 repetitions in an area of 1 cm^2^ with intervals of 1 s (wind-up response). The pain intensity measured with an NRS ranging from 0 (no pain) to 100 (most intense pain imaginable) for both the single repetition and the series is recorded in each of the seven body locations (see online supplementary material 1).^50 51^ The WUR (ratio) is calculated as: WUR=(NRS-10/NRS-1). If NRS-1 is 0, the WUR for that location cannot be calculated and it will be registered as a missing value. The WUR test according to the DFNS protocol has shown to have poor test–retest (r=0.67) and interobserver reliability (r=0.56).^44^

*Mechanical detection threshold* (*MDT*)—to test the ability to detect light touch—is assessed with a standardised set of von Frey filaments (OptiHair2-Set, Marstock Nervtest, Germany) with a modified method of limits.^52 53^ Starting at the intensity of 16 mN, the stimulus application progressively decreases until patients do not report any sensation. The intensity of the filament that is not perceived in millinewtons is recorded in each of the seven body locations (see online supplementary material 1).^54^ The MDT test, according to the DFNS protocol, has shown to have good test–retest (r=0.90) and interobserver reliability (r=0.89).^44^

*Pressure pain threshold* (*PPT*)—to test the ability to perceive pressure pain stimuli on muscles—is assessed with an electronic pressure algometer (Force Ten FDX, Wagner Instruments, USA). With this tool, the pressure in the contact point (1 cm^2^ tip) is progressively but steadily increased until patients report to feel pressure change towards painful (burning, drilling or aching). The intensity in newtons when pressure becomes painful and its pain intensity with an NRS ranging from 0 (no pain) to 100 (most intense pain imaginable) scale is recorded in each of the seven body locations (see online supplementary material 1).^32^ The PPT test according to the DFNS protocol has shown to have good test–retest (r=0.88) and interobserver reliability (r=0.84).^44^

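### Averaging the pinprick pain threshold over body sites in millinewtons over-weights the least sensitive sites and lets the score move with the sites present; per-site log and standardised values would be a cheap improvement

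*Protocol article*

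**What the plan says.** The Analyses section of the protocol article fixes the summary of every sensory test: "the overall value of each sensory test is the mean at the most painful location and the five control locations together". The condition attached to this rule is "provided that at most two locations are missing". A score can therefore rest on four, five or six sites.

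For MPT, the section on quantitative sensory testing describes "standardised weighted pinprick stimulators with seven different intensities". The procedure is: "Starting at the lowest intensity (8 mN), it progressively increases until patients report the stimulus to change from touch to painful". The value kept is in force units: "The intensity of the pinprick that produces the first painful stimulus in millinewtons is recorded in each of the seven locations" (the seventh is a training site and does not enter the mean). The wind-up test uses a "suprathreshold pinprick stimulator of 256 mN" from the same manufacturer's set, so the set contains both 8 mN and 256 mN.

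The list of variables to be calculated names the allodynia ratio, the wind-up ratio and conditioned pain modulation among the sensory tests. It does not name MPT, the mechanical detection threshold (MDT) or the pressure pain threshold (PPT), and no log scale or per-site standardisation is mentioned. For objective 3, scores are differenced between baseline and discharge.

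**The concern.** Seven stimulators that start at 8 mN and include 256 mN suggest roughly multiplicative steps. On such a scale an arithmetic mean in mN does not treat sites equally: a site one doubling higher counts twice as much. The patient's score then reflects the least sensitive sites more than the typical site.

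Because up to two of the six sites may be absent, the score also depends on which sites happen to be present. In a cross-sectional analysis this adds noise. In a change score it can appear as change where there is none, if the available sites differ between visits.

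What is at stake is some attenuation of the MPT associations. The article expects correlations between central sensitisation measures to be weak (0.25 in the sample size section), so there is little room for avoidable loss.

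**Working it through.** The article gives no figure for this score, so there is none to reproduce. The check is arithmetic on the stated rule, followed by a simulation for its typical size.

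**Range.** log2(256 / 8) = 5 doublings.

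**Weight of one high site.** Suppose five sites are at 16 mN and one at 256 mN (illustrative).
- Mean in mN: (5 × 16 + 256) / 6 = 336 / 6 = 56.0.
- Share of the high site: 256 / 336 = 76%, against 1/6 = 17% under equal weights.
- Mean on the log scale: 2^((5 × 4 + 8) / 6) = 2^4.67 = 25.4 mN.
- With the other five sites at 8, 32 or 64 mN, the share is 86%, 62% or 44%.

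**Shift with the sites present, same patient.**
- Raw: 16 mN if the high site is missing, up to (3 × 16 + 256) / 4 = 76 mN if two low sites are missing. Ratio 76 / 16 = 4.75.
- Log scale: 16 mN up to 2^((3 × 4 + 8) / 4) = 32 mN. Ratio 2.0.
- Change score: six sites at baseline (56) and the high site missing at discharge (16) give 16 − 56 = −40 mN with no change in sensitivity. Objective 3 counts a rise in thresholds as improvement, so this would read as worsening. Using only the five sites measured at both visits gives 16 − 16 = 0.

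**A milder pattern.** Sites at 32, 32, 64, 64, 128 and 128 mN, with the two highest lost.
- Raw: 448 / 6 = 74.7 falls to 192 / 4 = 48, a drop of 36%.
- Log scale: 2^6 = 64 falls to 2^5.5 = 45.3, a drop of 29%.

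Logging alone therefore does little for missing sites here.

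**Typical size.** The documents give no spread of MPT between patients or sites, so these inputs are assumptions:
- between-patient SD of 1 or 1.5 doublings;
- random between-site SD of 0.5 to 1.5 doublings;
- systematic site differences of 0 or 2 doublings across the six sites;
- top of the set at 256 or 512 mN, with thresholds rounded up to a doubling grid.

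Sixteen scenarios of 100,000 simulated patients were run. Six of them:

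| Top (mN) | Patient SD | Site SD | Systematic | Median share of highest site | Patients with one site above half | r raw | r log | (r log / r raw)² |
|---|---|---|---|---|---|---|---|---|
| 256 | 1 | 0.5 | 0 | 24% | 0% | 0.914 | 0.969 | 1.12 |
| 256 | 1.5 | 1 | 2 | 31% | 7% | 0.916 | 0.945 | 1.06 |
| 256 | 1 | 1.5 | 2 | 35% | 14% | 0.802 | 0.831 | 1.07 |
| 512 | 1 | 0.5 | 0 | 25% | 0% | 0.872 | 0.973 | 1.25 |
| 512 | 1.5 | 1 | 0 | 31% | 4% | 0.867 | 0.955 | 1.21 |
| 512 | 1 | 1.5 | 2 | 40% | 25% | 0.778 | 0.843 | 1.17 |

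Here r is the correlation of the score with the patient's true level on the log scale. Over all sixteen scenarios r runs from 0.78 to 0.93 raw and from 0.83 to 0.97 logged. Further variation of the assumptions widens this to about 0.76–0.95 and 0.83–0.98, with a squared ratio (relative effective sample size) of 1.03 to 1.29. If the logged score correlated 0.25 with an outcome, the raw score would correlate between 0.25 / √1.29 = 0.22 and 0.25 / √1.03 = 0.246.

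With two sites missing at random, the raw score moves by a median factor of 1.07 to 1.23. The 95th percentile is 1.24 to 2.15 raw and 1.26 to 1.78 on the log scale.

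**Later safeguards.** The 3 SD rule, Cook's distance, leverage, the optional Spearman coefficient and the regression assumption checks all act on the patient's overall value. None restores equal weighting of the sites within a patient.

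**The case against.** Much can be said for the plan as written.

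- The article fixes the mean but not, in so many words, its scale, and a fuller plan may specify a transformation. The list of calculated variables is also not exhaustive, since it omits the CSI sum score. This stands as a caveat: the raw scale is the plain reading, not a stated fact.
- A reader might infer that one insensitive site dominates the score. The documents do not support that in general. It needs one site about three or more doublings above the rest; under the assumed spreads a single site exceeds half the total in 0% to 25% of patients.
- A reader might also infer that every sensory-test association is attenuated. That is not supported either. The wide range is documented for MPT only: the article gives just a 16 mN starting point for MDT and no range for PPT, and the other tests are ratios or a percentage. QST proxies are chosen by the strongest correlation with each functioning measure, so MPT may enter few regression models or none.
- The only stated reason for a missing site value is a zero first rating, which concerns the allodynia and wind-up ratios. How often MPT sites will be missing is unknown, and the examples above choose unfavourable patterns.
- The simulation defines true sensitivity on the log scale, which favours the log mean. At the low end the gain is negligible.
- A skewed score is not unguarded, because leverage and Cook's distance are planned for outlying cases. These act after averaging, so they leave the weighting as it is.

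These points limit the scope and size of the concern. They do not remove the unequal weighting of MPT or its dependence on the sites present.

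**Conclusion.** The point holds as a cheap improvement for MPT, not as an error that threatens the study. On the plain reading, the mean in mN gives the highest site about a quarter to 40% of the total instead of 17%, and it shifts when different sites are available. The consequence is clearest in the objective 3 change scores, where a different set of sites at discharge can pass for change.

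The loss of information is consistent in direction but modest: the correlation with log-scale sensitivity is about 0.76–0.95 raw and 0.83–0.98 logged. Those figures rest entirely on assumed spreads, a doubling grid and a log-scale definition of sensitivity. Extension to MDT and PPT is conditional on their site values proving similarly skewed.

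**What to change.** In the data preparation, before averaging:

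1. Take the logarithm of MPT at each site. Do the same for MDT and PPT if their site values are similarly skewed.
2. Standardise within each site across patients, using the baseline mean and SD at both visits so that change is preserved.
3. Average the available standardised values under the existing allowance for missing sites.
4. For change scores, use only sites measured at both visits. With two different sites missing at each visit, only 6 − 2 − 2 = 2 would be shared, so apply the same allowance (at least four sites) to the shared set.

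Standardisation removes systematic differences between sites, not a patient's own site-to-site variation. The most painful site is chosen by the patient and so is not anatomically uniform; its standardised value needs that caveat.

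The cost is a few lines of code, the loss of some patients from the change analysis under step 4, and a score in standardised units. Raw values in mN or N should still be reported descriptively. If the sponsor prefers to keep the present mean, stating its scale and adopting step 4 would be the minimum.
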